## Methods/Design

### Aims

The PALM cohort study will establish and follow-up a cohort of mother-child pairs who had a prenatal diagnosis of a CNV from 2013-2019 (inclusive) in the Australian state of Victoria. Victoria has approximately 78,000 births per year and a median maternal age of 31.5 years [13]. Approximately 2-3% of all pregnant women undergo prenatal diagnosis per year [14].

The study aims are to:
Compare the developmental, social-emotional and health status of children with a prenatal diagnosis of a prenatal CNV with those children with no CNV detected on CMA.Measure the impact of a prenatal diagnosis of a CNV on maternal perceptions of child health, behavior, and development.Determine the proportion of CNV ascertained prenatally that are reclassified from unknown or uncertain to benign or pathogenic after two or more years using contemporaneous curation resources.

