Quantitative survey	‘Younger cohort’ children who are 12-30 months old at the time of enrolment	Ages and Stages Questionnaire-3	Parent	Online or hard copy. 20-30 minutes.
		Ages and Stages Questionnaire Social Emotional-2	Parent	
Quantitative survey	‘Older cohort’ children who are 2 years 7 months to 7 years 7 months at the time of enrolment	The Vineland-II Adaptive Behavior Scale (VABS)	Parent	Online or hard copy. 20-60 minutes
Psychologist assessment		Wechsler Preschool and Primary Scale of Intelligence IV (WPPSI-IV)	Psychologist	In person. 20-60 minutes
Clinical assessment		Clinical assessment by study pediatrician: measurements of height, weight, and head circumference; history and physical examination	Paediatrician	In person. 20-60 minutes
**Outcome 3:** The frequency of copy number variants that have a change in classification after reanalysis after ≥2 years will be presented in a descriptive analysis. For the participants in the reanalysis group, an additional letter will be sent to them with the results of the updated analysis.				
Clinical standard laboratory software and databases in use during 2021-2022	Children who were prenatally diagnosed with a copy number variant of uncertain or unknown significance	Affymetrix Chromosome Analysis Suite (ChAS) software	Cytogenetics Laboratory	n/a
		DatabasE of Chromosomal Imbalance and Phenotype in Humans using Emsembl Resources (DECIPHER)	Cytogenetics Laboratory	
		International Standards for Cytogenomic Arrays (ISCA) database	Cytogenetics Laboratory	
		Online Mendelian Inheritance in Man (OMIM)	Cytogenetics Laboratory	

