#### For the 12–24-month-old group, the ASQ-3 and ASQ:SE-2 scores are the primary outcomes

Scores for individual items are summed to give an overall continuous score for each of the domains in the ASQ-3 and ASQ:SE-2. In addition to using scores as continuous outcomes, we will categorize the scores according to the recommended scores for typical development, need for monitoring, and need for further assessment. We will collapse these three categories into a binary variable (those with typical development vs those with a need for monitoring or further assessment [i.e., potential atypical or delayed development]). The differences in those with typical and ‘atypical’ scores will be compared among the CNV subgroup using chi-squared test for proportions or Fisher’s exact test as appropriate.

#### Objective 2

The primary outcome will be the BITSEA score. We will analyze the data according to the subgroup of CNV result (pCNV, VUS) compared with controls, stratified by age. The secondary outcomes will be the Maternal Postnatal Attachment Questionnaire (MPAS), Vulnerable Child Scale (VCS), Profile of Mood States (POMS), and the Parent Sense of Competence Scale (PSOC). For the secondary outcomes, we will compare group differences in responses using mixed effect regression models. We will report mean values for the parent report of child behavior, parenting competence, attachment, perceived child vulnerability and parent mood. Parent gender, country of birth, education, employment status, and child sex will be adjusted as covariates.

#### Objective 3

We will compare the classifications given at the time of issue of the prenatal report and the current classifications in 2020-21 according to the issuing laboratory’s protocols. The proportion of pCNVs, VUS and benign variants will be compared between the prenatal and 2-year postnatal classifications using chi-squared test for proportions.

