### Dealing with rapidly evolving knowledge base

Genomic knowledge is accelerating, and fetal VUS may be reclassified as benign or pathogenic as clinical evidence accumulates and annotation resources are updated. Reanalysis of CNVs in the NICHD prenatal microarray cohort after three years showed a dramatic reduction in the numbers of VUS from 94 to 35, and a corresponding increase in pathogenic CNVs (pCNVs) (from 35 to 70) and ‘likely benign’ CNVs (from 36 to 60) [37]. An Australian study of a pediatric cohort that was evaluated with CMA in 2010 showed a statistically significant increase in potentially pathogenic results from 19% to 31% upon reanalysis in 2012 [38]. There is currently no guidance on whether a prenatal CNV should be reinterpreted in the postnatal period and whose responsibility it is to contact parents in the case of a change in classification [39]. This study will provide information to help guide clinical practice recommendations about postnatal review and follow-up.

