### Translation plan

Translation plan for this research will depend on the final results. We anticipate that there may be new recommendations for clinical practice, including:
Structured follow up for children diagnosed prenatally with VUS,Offer parents the option of re-analysis of the CMA result after 2 years postnatal ageDevelopment of patient information resources for pregnant women and their partners after receiving a result of uncertain significanceUpdating of existing genomic annotation resources such as DatabasE of Chromosomal Imbalance and Phenotype in Humans using Ensembl (DECIPHER) with new genotype-phenotype correlations

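### Objective 3 calls a single calendar-time re-reading the two-year postnatal classification, although the plan's own dates give intervals from about 0–1 to 9–10 years

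*Protocol article*

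**What the plan says.** The Aims section sets out to find the proportion of prenatally found variants "reclassified from unknown or uncertain to benign or pathogenic after two or more years". Table 2 (Data collection, Outcome 3) agrees with that floor: "a change in classification after reanalysis after ≥2 years will be presented in a descriptive analysis". Both describe a minimum interval, not a fixed time point.

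Objective 3, in the section on statistical methods and power, compares the classification on the prenatal report with "the current classifications in 2020-21 according to" the issuing laboratory's protocols. Its next sentence says that the proportions "will be compared between the prenatal and 2-year postnatal classifications", using a chi-squared test. Table 2 dates the re-reading differently: "Clinical standard laboratory software and databases in use during 2021-2022". The Inclusion criteria admit results reported from January 2013 to December 2019. The article describes no reading at a fixed age of two years.

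The Discussion supplies the reason for re-reading: "fetal VUS may be reclassified as benign or pathogenic as clinical evidence accumulates". The Translation plan lists an offer of re-analysis after two years of postnatal age among possible outputs, introduced by: "We anticipate that there may be new recommendations for clinical practice".

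**The concern.** A two-year classification and a re-reading of every eligible variant in one calendar window are different quantities. A 2013 report is re-read seven or more years later, and a late-2019 report after two or three years at most. One pooled proportion mixes these intervals, and its value depends on how many enrolled families come from each testing year.

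If the result is published under the two-year label, readers will take it as the yield of re-analysis at about two years. That is also the age named in the Translation plan. Laboratories and parents weighing re-analysis at that age could then be given a figure that describes a typical interval of about five years.

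**Working it through.** **Inputs.** Report dates January 2013 to December 2019 (Inclusion criteria); re-reading in 2020-21 (Objective 3) or 2021-2022 (Table 2); 94 uncertain variants falling to 35 after three years in the US cohort (Discussion, on the evolving knowledge base); 267 expected participants with an uncertain variant (Sample size). Assumptions: reports spread evenly over the seven years, and re-reading spread evenly over the two-year window. Where time is counted from birth, birth is taken as 0.4 or 0.55 years after the report.

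**Step 1: can the two-year label be reproduced?** Interval = re-reading date − report date.

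| | 2020-21 | 2021-2022 |
|---|---|---|
| Shortest (years) | 2020 − 2020 = 0 | 2021 − 2020 = 1 |
| Longest (years) | 2022 − 2013 = 9 | 2023 − 2013 = 10 |
| Mean (years) | 2021 − 2016.5 = 4.5 | 2022 − 2016.5 = 5.5 |
| Share at 1.5–2.5 years | 13–14% | 7–11% |
| Share over 3 years | 64–71% | 78–86% |
| Share under 2 years | 14–22% | 4–9% |

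The ranges reflect counting from report or from birth. Neither window gives a two-year interval, and both admit some variants below the two-year floor.

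**Step 2: what could this do to the yield?** For illustration, take a constant rate *h*, so that the proportion reclassified by time *t* is 1 − exp(−*ht*). The US figures give *h* = −ln(35/94)/3 = 0.329 per year. Two lower rates are assumed: 20% over three years, −ln(0.8)/3 = 0.074, and 10% over three years, −ln(0.9)/3 = 0.035. With a re-reading window that opens at the end of 2019, the mean over intervals is

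pooled = 1 − [(1 − exp(−2*h*))/(2*h*)] × [(1 − exp(−7*h*))/(7*h*)].

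At *h* = 0.329 this is 1 − 0.733 × 0.391 = 0.714. A window one year later multiplies the subtracted product by exp(−*h*), giving 0.794.

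| Rate per year | At 2 years from report | At 2 years postnatal (2.4 from report) | Pooled, 2020-21 | Pooled, 2021-2022 |
|---|---|---|---|---|
| 0.329 | 48.2% | 54.6% | 71.4% | 79.4% |
| 0.074 | 13.8% | 16.3% | 27.6% | 32.8% |
| 0.035 | 6.8% | 8.1% | 14.4% | 17.3% |

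The smallest ratio is 71.4/54.6 = 1.3 and the largest 17.3/6.8 = 2.5. Dropping intervals under two years moves this range only slightly, from 79.4/54.6 = 1.5 (2020-21, counted from birth) to 17.8/6.8 = 2.6 (2021-2022, counted from report).

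**Step 3: the opposite case.** If all reclassification accrues evenly over the first two years after the report and then stops, the pooled figure over all variants is 0.95 (2020-21) or 0.99 (2021-2022) times the two-year figure. There is then no overstatement.

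**The case against.** The aim is worded correctly. Two or more years is a legitimate descriptive target, and the sentence just before the disputed label gives the true comparison with current classifications. On this view the label is loose shorthand in one sentence. That stands as far as pooling goes: combining long intervals follows from the aim and is not itself an error.

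A reader might infer that the study is committed to recommending re-analysis at two years. The Translation plan does not support that. It makes its outputs depend on the results and says only that recommendations may follow, and an offer after two years can mean any later time. The Discussion asks more broadly whether a prenatal variant should be reinterpreted after birth at all.

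A reader might also infer that the pooled figure is bound to overstate the two-year yield. The article offers only a qualitative premise and one net change at three years in another cohort, which cannot show whether reclassification continues or levels off. The intervals under two years admitted by the 2020-21 window also pull the pooled figure down.

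Finally, time strata and confidence intervals are details that an article may leave to a fuller document, so their absence is not the fault raised here. None of these points makes the two-year label agree with the dates.

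**Conclusion.** The mislabelled time point stands. Under either stated window the mean interval from report is about 4.5 to 5.5 years, the longest is about 9 to 10, and only about 7–14% of variants lie near two years. These shares assume evenly spread reports and re-readings; the extremes of the range follow from the dates alone. With the 2020-21 window, about 14–22% of variants would also miss the aim's own floor.

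The effect on the result is conditional. If reclassification continues to accrue, as the Discussion suggests, reading the pooled proportion as a two-year figure overstates the two-year yield by a factor of about 1.3 to 2.5, depending on the assumed rate, the window, and whether time is counted from report or birth. The factor is illustrative, and the overstatement vanishes if reclassification is complete by two years. The point deserves correction before reporting. It does not undermine the ≥2-year aim.

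**What to change.** 1. In Objective 3, replace the two-year postnatal label with ≥2 years after the prenatal report.
2. Reconcile the re-reading window between Objective 3 (2020-21) and Table 2 (2021-2022), and say how variants re-read before two years are handled.
3. Beside the pooled ≥2-year figure, report the proportion of uncertain variants reclassified to pathogenic and to benign by time since report, with confidence intervals: for example under 2 years if any, 2–3, 4–5, and 6 or more.
4. Base any statement about re-analysis at about two years on the shortest eligible stratum.
5. Note that, with one re-reading window, time since report and year of report cannot be separated.

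No new data are needed, because pre-screening stage 1 shows that the database holds the date of testing. The cost is wording and some precision. If 267 uncertain variants are spread evenly over seven years, a two-year band holds 267 × 2/7 ≈ 76. The widest 95% interval is then 1.96 × √(0.25/76) ≈ ±11 percentage points.

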## Discussion

This cohort study addresses four current areas of uncertainty in practice, including

### Lack of choice in amount of fetal genomic information received

We have previously shown that when given a choice about receiving different levels of genomic information from prenatal CMA, 40% of Australian pregnant women choose NOT to have extended information that might include VUS [35]. However, outside this research protocol, reporting on VUS remains standard laboratory practice, irrespective of patient preference. Our study will provide new data on the postnatal outcomes of VUS which may help inform the clinical utility of revealing this information during pregnancy.

### Women’s experience of prenatal VUS

While most children with VUS are expected to have normal outcomes, the possibility of an increased risk of developmental disorder can result in parental anxiety, termination of healthy pregnancies, “hypervigilant” parenting styles, and increased utilization of medical services [36]. A prenatal diagnosis of a VUS may also alter early parental perceptions of the competency of the child [16]. Our study will be able to determine whether there are any such ‘harms’ associated with the disclosure of VUS, and enable us to develop strategies to mitigate these negative effects.

### Dealing with rapidly evolving knowledge base

Genomic knowledge is accelerating, and fetal VUS may be reclassified as benign or pathogenic as clinical evidence accumulates and annotation resources are updated. Reanalysis of CNVs in the NICHD prenatal microarray cohort after three years showed a dramatic reduction in the numbers of VUS from 94 to 35, and a corresponding increase in pathogenic CNVs (pCNVs) (from 35 to 70) and ‘likely benign’ CNVs (from 36 to 60) [37]. An Australian study of a pediatric cohort that was evaluated with CMA in 2010 showed a statistically significant increase in potentially pathogenic results from 19% to 31% upon reanalysis in 2012 [38]. There is currently no guidance on whether a prenatal CNV should be reinterpreted in the postnatal period and whose responsibility it is to contact parents in the case of a change in classification [39]. This study will provide information to help guide clinical practice recommendations about postnatal review and follow-up.

### Lack of structured follow up for children at risk of developmental disorders

There is no standardized approach to identifying and following up infants after a prenatal diagnosis of VUS in Australia. These infants may be at increased risk of poor outcome, yet there is no translation of this knowledge into clinical practice. This study will provide the outcomes required to understand the potential need for structured developmental follow-up.

### Translation plan

Translation plan for this research will depend on the final results. We anticipate that there may be new recommendations for clinical practice, including:
Structured follow up for children diagnosed prenatally with VUS,Offer parents the option of re-analysis of the CMA result after 2 years postnatal ageDevelopment of patient information resources for pregnant women and their partners after receiving a result of uncertain significanceUpdating of existing genomic annotation resources such as DatabasE of Chromosomal Imbalance and Phenotype in Humans using Ensembl (DECIPHER) with new genotype-phenotype correlations

### Potential risks related to study conduct

#### Creation of new clinically relevant information during the study

There are several potential opportunities for information to be disclosed that may require clinical action.

#### Poorer than expected results on the developmental assessments

Participants will be given a summary report on their child’s results by email or standard mail (as preferred) with a qualitative description of their child’s scores. They will be encouraged to contact the study coordinator if they have concerns regarding the report and they may have the full results sent to their child’s healthcare provider or the education provider following receipt of a signed consent form. If the participant requires a follow-up or a new referral to a clinical service, our study pediatrician or psychologist will facilitate this for them.

Reclassification of the child’s genomic variant by the laboratory may bring benefits (e.g., reassurance if a VUS has been reclassified as benign) or potential harms (it may cause further anxiety if the presumed cause of a child’s phenotype is no longer considered contributory, or it has been reclassified from ‘uncertain significance’ to ‘likely pathogenic’). For this reason, all CNVs will be reported to the participant regardless of the ‘direction’ of reclassification (increased or decreased clinical significance, or no change in classification). The results will be sent with a cover letter with information on how to contact our study coordinator if they have any questions or concerns. The results will be shared with their nominated health care provider after signed consent to share information. If the participant requires a referral to a clinical service, our study pediatrician or psychologist will facilitate this for them.

#### Distress caused by contacting women who have experienced a child death or stillbirth

Our pre-screening steps are time-consuming and resource-intensive but essential to minimize the risk of contacting women who have had a termination of pregnancy, perinatal loss or child death. However, we cannot eliminate the possibility of accidently sending invitation letters to women whose child has died and thus potentially causing emotional distress. We have designed the most feasible prescreening process available under the current constraints.

#### Poor recruitment

We have based our uptake rates on those experienced in a similar multicenter follow up study in the United States, and therefore believe these to be realistic. However, it is possible that we will not meet our recruitment targets either due to higher-than-expected ineligibility rates, missing data, or study acceptability. If that occurs, we will endeavor to pool our data with the United States cohort as we have harmonized our outcome measures to facilitate this if needed. Permission for data sharing outside Australia has been included as an option in the consent form.

### Summary

The PALM study is the first Australian study to follow up a cohort of mother-child pairs to assess the long-term developmental, social-emotional and health outcomes of children diagnosed before birth with a genomic CNV on CMA. We expect that this will improve our care of families by providing evidence to guide pre-and postnatal medical care, and to mitigate the negative consequences of conveying genomic uncertainty during pregnancy.

## Data Availability

Not applicable.

## Abbreviations

AE: Adverse Event
ASQ:SE-2: Ages and Stages Questionnaire: Social-Emotional-2
ASQ-3: Ages and Stages Questionnaire, third edition
BEMAPRE: Belgium MicroArray Prenatal Microarray consortium
BITSEA: Brief Infant-Toddler Social and Emotional Assessment
BRIEF: Behavior Rating Inventory of Executive Function
BRIEF-P: Behavior Rating Inventory of Executive Function – Preschool version
ChAS: Chromosome Analysis Suite
CSHCN: Children with Special Health Care Needs screener
CMA: Chromosomal microarray
CNV: Copy number variant
CVS: Chorionic villus sampling
DECIPHER: DatabasE of Chromosomal Imbalance and Phenotype in Humans using Ensembl Resources
DGV: Database of Genomic Variation
GRIMS: Golombok Rust Inventory of Marital State
HREA: Human Research Ethics Application
HREC: Human Research Ethics Committee
ISCA: International Standards for Cytogenomic Arrays
MCRI: Murdoch Children’s Research Institute
MHW: Mercy Hospital for Women
MMC: Monash Medical Centre
MPAS: Maternal Postnatal Attachment Questionnaire
NHMRC: National Health and Medical Research Council
NICHD: National Institute of Child Health and Human Development
PALM: PrenatAL Microarray
pCNV: Pathogenic copy number variant
PHQ-8: Patient Health Questionnaire Depression scale-8
PI/CPI: Principal Investigator / Coordinating Principal Investigator
PICF: Participant Information and Consent Form
POMS: Profile of Mood States
PSOC: Parent Sense of Competence Scale
RCH: Royal Children’s Hospital (Melbourne)
RGO: Research Governance Office
RWH: Royal Women’s Hospital (Melbourne)
SDQ: Strengths and Difficulties Questionnaire
SEHQ: School Entrant Health Questionnaire
SoA: Schedule of Assessments
VABS: Vineland-II Adaptive Behavior Scale
VCGS: Victorian Clinical Genetics Services
VCS: Vulnerable Child Scale
VPDC: Victorian Perinatal Data Collection
VPDD: Victorian Prenatal Diagnosis Data collection
VUS: Variants of uncertain/unknown significance
WPPSI-IV: Wechsler Preschool and Primary Scale of Intelligence IV
